## Results

Although the trial is ongoing, recruitment has already begun. As of the time of submission, 22 participants have been enrolled and have completed the diagnostic eligibility assessment. Data collection started in 2022 following the training of participating therapists in the use of the SNS, which was funded by the German Society for Autosystemic Hypnotherapy in 2022 and 2025. Data collection will continue until all follow-up assessments (T4) are completed, which is projected for the first quarter of 2027. No outcome analyses have been conducted to date. Study findings are expected to be disseminated in the second quarter of 2027.

## Discussion

### Principal Findings

This study tries to combine the strictness of an RCT with the ecological validity of routine care (outpatient settings). The aims of this study focus on the effectiveness of ASH and of ASH improved by personalized high-frequency monitoring and feedback, which was technologically implemented by the SNS. This kind of comparison has never been conducted in an RCT under real-world conditions, and the combination of outcome and process research from the perspective of nonlinear complex systems [10,62] is an innovative step in psychotherapy research.

Besides the frequency of patients’ self-assessments, the frequency and quality of feedback sessions (participative interviewing and shared decision-making) also matter. Studies have shown that information from feedback is often not used in clinical practice. Although routine outcome monitoring is mandatory in many countries, measuring outcomes (or even processes) does not necessarily mean that this information is being used to inform or to advance the treatment. Even in RCTs, up to half of the clinicians do not use progress feedback to inform treatment decisions [8,63]. In a specific RCT [64], one third of the clinicians reportedly never viewed any progress feedback reports. In a content analysis of written notes [65], clinicians included in the study incorporated feedback data in only about one-fifth of the sessions. A review addressing the barriers to implementing precision methods as feedback in personalizing psychological therapies, and possible solutions, has been published recently [66]. This study investigates an optimal way of implementing feedback in clinical practice (outpatient therapy) and integrating it into treatment as usual.

The combined structure of this study’s design should allow differentiation between patient effects, therapist effects, and different degrees of preferences for the feedback method (SPM). In contrast to pharmaceutical trials, patients and therapists know what they should do and are proactively involved in the treatment. This involvement is not a bias that has to be eliminated; it might rather be an active ingredient of a successful psychotherapy in which the therapists and the patients take a proactive and collaborative role in the treatment plan.

### Bias Minimization

At the level of patients and therapists, biases should be minimized. Patients will be randomly assigned to conditions to reduce systematic selection biases in participant characteristics. The inclusion and exclusion criteria allow for a relatively homogeneous group of individuals with depression-anxiety spectrum diagnoses, and by measuring the psychotherapy motivation at the beginning of the treatment period (T2), motivation biases can be considered (statistically balanced). At the therapist level, a potential bias due to the therapist’s preferences is a concern because of outcome expectations, which can be impactful for patients and for therapists. In the proposed design, potential therapist effects can be considered (statistically balanced), and the present ABAB crossed therapist design can consider the preferences of realizing the SPM procedure.

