**Methods:**

This study is a randomized controlled trial with 2 arms, using within-therapist randomization (ABAB design) in outpatient psychotherapy. Participants are recruited offline via routine intake procedures. A total of 100 patients will be randomly assigned to one of the two conditions following a waiting period. The inclusion criterion is the existence of any mood disorder (major depressive disorder or anxiety disorder), assessed via a clinical interview. Each therapist treats patients in both conditions. Outcomes will be measured at 4 time points: after diagnosis confirmation, postwaiting period, posttreatment, and a 6-month follow-up. Primary and secondary outcomes, including symptom severity, will be assessed using questionnaires. Data collection also includes patient and therapist session evaluations using the Bern Patient and Therapist Session Questionnaire. In the feedback condition, therapists conduct frequent interviews using time-series data generated from daily self-assessments using the synergetic navigation system, including the Therapy Process Questionnaire and an individualized measure based on case conceptualization.

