## Methods

### Study Design

This study is designed as an RCT with 2 arms, using within-therapist randomization in the real-world clinical practice of routine outpatient psychotherapy in Germany.

Participants are recruited offline through routine intake procedures when presenting for outpatient psychotherapy with participating therapists. Patients who are suspected by the therapist to meet criteria for MDD, AD, or MDD with anxious disorders complex will be briefly screened for their ability and willingness to use a smartphone. If eligible, they will be informed about this study and its requirements by the respective therapist and asked whether they are interested in participating in a research project. Afterward, they will be informed of the procedure and the requirements of this study by the respective therapist. They obtain a flyer with basic information and, in case of concrete interest, will be instructed in detail and obtain an explanation to its full extent.

Patients who have consented to participate in this study will undergo a structured diagnostic interview (Structured Clinical Interview for *DSM-5* [*Diagnostic and Statistical Manual of Mental Disorders* {Fifth Edition}] – Clinician Version) [41] to confirm the inclusion criteria (diagnoses as listed in the Participants section, see below). The interview will be conducted remotely by an independent, trained clinical psychologist who is otherwise not involved in this study. The Structured Clinical Interview for *DSM-5* allows a final decision on including or excluding the patient. In addition to diagnostic confirmation, baseline information on participants’ current medication, concurrent treatment, and symptom severity will be systematically assessed. These variables will be considered as covariates in the main outcome analyses to account for potential prognostic influences. In addition, sensitivity analyses will be conducted to examine whether excluding participants with concurrent treatments or psychopharmacological medication changes affects the robustness of the findings. Following inclusion, a waiting period of 1 (minimum) to 6 months (maximum) begins for each patient, depending on the therapist’s capacity to initiate treatment.

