### Participants

As this study involves self-assessments via a smartphone application of the SNS, participants are required to have basic smartphone and internet literacy. This is assessed informally during the initial instruction and onboarding process by the respective therapist.

The patients who will be included in this study should be diagnosed with a spectrum of depression and ADs as listed in the *ICD-10* (*International Statistical Classification of Diseases, Tenth Revision*) [43], which is still valid in Germany. These are F32 depressive episode, F33 recurrent depressive disorder, F34 persistent mood disorders, F40 phobic ADs (eg, agoraphobia, social phobia, and specific phobias), F41 other ADs (eg, panic disorder, GAD, mixed anxiety and depressive disorder), F43 reaction to severe stress and adjustment disorders, and F45 somatoform disorders. At least one of these categories should be identified as the main diagnosis; other diagnoses (comorbidities) will be accepted. The reason for focusing on these diagnoses is their high prevalence rates and in consequently, the frequency of occurrence in routine outpatient psychotherapy. Exclusion criteria are aged younger than 18 years, acute suicidality, mental confusion, intoxication by drugs, substance use, and severe neurological diseases.

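### The sample is called relatively homogeneous although seven ICD-10 groups qualify, and main diagnosis is not among the covariates named for the main outcome analyses: a small, avoidable loss of precision, not a bias

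*Protocol article*

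**What the plan says.** The claim of homogeneity stands in the Discussion, under Bias Minimization, as one of several patient-level measures: "The inclusion and exclusion criteria allow for a relatively homogeneous group of individuals with depression-anxiety spectrum diagnoses". The sentence before it names randomisation: "Patients will be randomly assigned to conditions to reduce systematic selection biases in participant characteristics". The same sentence goes on to say that motivation measured at T2 allows motivation bias to be taken into account.

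The Participants section lists F32, F33, F34, F40 and F41, then "F43 reaction to severe stress and adjustment disorders, and F45 somatoform disorders". It continues: "At least one of these categories should be identified as the main diagnosis; other diagnoses (comorbidities) will be accepted". The limits are these: "Exclusion criteria are aged younger than 18 years, acute suicidality, mental confusion, intoxication by drugs, substance use, and severe neurological diseases". The Abstract describes a narrower population: "The inclusion criterion is the existence of any mood disorder (major depressive disorder or anxiety disorder), assessed via a clinical interview".

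On analysis, the Study Design section says that at baseline "current medication, concurrent treatment, and symptom severity will be systematically assessed", and then: "These variables will be considered as covariates in the main outcome analyses to account for potential prognostic influences". Main diagnosis is not in that set, although the structured interview confirms each patient's qualifying diagnosis before inclusion. The same section describes block randomisation within therapist and mentions no stratification by diagnosis.

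**The concern.** The two descriptions of the sample do not fit. Two of the seven groups, F43 and F45, are by their own titles neither depressive nor anxiety disorders. The reason given for the list, that these diagnoses are common in routine outpatient care, is a reason for breadth.

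The primary outcomes are symptom scales aimed at depression and anxiety. The amount of change they can show may plausibly differ between patients whose main problem is depressive, phobic or somatoform. If it does, and diagnosis is neither balanced nor adjusted for, that variance stays in the error term of the arm comparison. Precision is what is at stake, in a trial planned at 80% power for this comparison.

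**Working it through.** **1. The plan's own figures.** Inputs from Power Considerations: f = 0.25, two levels (m = 2), correlation ρ = 0.50, power 0.80, stated N = 98. Alpha is not given; 0.05 is assumed. For the between-subject factor in a repeated-measures ANOVA:

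- λ = f²·N·m / (1 + (m − 1)ρ), with 1 and N − 2 degrees of freedom.
- N = 98: λ = 0.0625 × 98 × 2 / 1.5 = 8.17, power 0.808. At N = 96 power is 0.799, so 98 is the smallest even N that reaches 0.80. The stated figure reproduces.
- N = 100: λ = 8.33, power 0.816.
- Cross-check of the within-subject figure, λ = f²·N·m / (1 − ρ): 0.34² × 32 × 2 / 0.5 = 14.8, power 0.961 against the stated 96%.

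**2. Adding main diagnosis as a covariate.** Let R² be the share of residual variance that diagnosis explains beyond symptom severity. The article gives no value, so a range is assumed. Then λ becomes λ / (1 − R²). Three diagnosis groups cost 2 degrees of freedom; all seven would cost 6.

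| Assumed R² | λ at N = 100 | Power, 2 df lost | Power, 6 df lost | N for 80% power |
|---|---|---|---|---|
| 0 | 8.33 | 81.5% | 81.5% | 98 |
| 2% | 8.50 | 82.3% | 82.3% | 96 |
| 5% | 8.77 | 83.4% | 83.4% | 92 |
| 10% | 9.26 | 85.4% | 85.3% | 88 |
| 20% | 10.42 | 89.2% | 89.1% | 78 |

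The required N is the same for either coding. Against 98, the saving is 0 patients at R² = 0, 6 at 5% and 10 at 10%. The 20% row is an upper extreme, since severity is already in the model.

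**3. Chance imbalance.** Split 100 patients 50/50, with K of them in a given diagnosis group, ignoring therapist blocks. The SD of the arm difference in that group's share is (2/50)·√[50·(K/100)·(1 − K/100)·(50/99)]. For K = 10, 20, 30 and 50 this is 6.0, 8.0, 9.2 and 10.1 percentage points. If the group differs from the rest by 0.3 to 0.8 SD in outcome (assumed), a one-SD imbalance shifts the contrast by 0.3 × 0.060 = 0.02 SD up to 0.8 × 0.101 = 0.08 SD. For comparison, the planned effect is d = 2f = 0.50, and the standard error of a simple two-arm mean difference on one measurement is √(2/50) = 0.20 SD.

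**4. Type I error.** A simulation of 20,000 null trials, with seven groups of different prognosis, 50 patients per arm and an unadjusted t test, rejected in 5.2%. That is nominal within simulation error.

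**The case against.** The strongest reply is that this is one loose phrase in a discussion plus a preference for a further covariate. Several parts of that reply stand.

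- A reader might infer that control of bias depends on homogeneity. It does not: randomisation is named first, and heterogeneity of prognosis does not bias a randomised comparison. Chance imbalance is already counted in the standard error, as the simulation shows.
- A reader might infer that the plan does nothing about heterogeneity. Symptom severity is a named covariate, and the analysis compares waiting-period change with treatment change within each patient, which removes stable differences in level. Only the remainder is at issue.
- A reader might infer that any comorbidity is allowed. The exclusions, such as substance use and severe neurological disease, limit this. The Participants section also places all seven groups under its own depression and anxiety spectrum, and the phrase says only relatively homogeneous.
- A reader might infer that diagnosis will certainly be ignored. The article does not show that. It mentions further covariates elsewhere (waiting time under Limitations, motivation under Bias Minimization, therapist preference under Statistical Analysis), and a complete list may stand in an analysis plan that is not shown.

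What the reply does not remove is the mismatch between the two descriptions of the sample, or the fact that the stated set for the main outcome analyses leaves out a variable established for every patient before inclusion.

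**Conclusion.** The point holds as a minor one. The homogeneity wording does not fit the eligibility list, and adding main diagnosis to the stated covariates would be a cheap gain in precision. For an added R² of 0 to 10%, power at 100 patients goes from about 81.6% to between 81.5% and 85%, or about 0 to 10 patients.

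This rests on alpha = 0.05, on the assumed R² beyond severity, and on the plan's own between-subject power model. A reader might infer that the planned 98 is too small. The documents do not support that: the figure reproduces, and f = 0.25 is a standardised assumption that already refers to whatever spread the sample has.

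**What to change.** Reword only the first clause of the Bias Minimization sentence so that it describes the range of diagnoses actually admitted. Keep the second clause: the T2 motivation measure is a separate and valid control. The population wording in the Abstract can be brought into line at the same time.

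Beside the covariates named under Study Design, prespecify main diagnosis group from the inclusion interview as a fixed covariate for the arm comparison, for example in three groups: F32–F34, F40–F41 and F43/F45.

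The cost is one sentence in the analysis section and two degrees of freedom, with no new data collection. The Results section reports that no outcome analyses have been done, so the choice can still be made independently of the outcome data. If diagnosis explains nothing beyond severity, there is no gain and power falls by about 0.02 percentage points (0.8155 to 0.8154).

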### Limitations

Despite all the measures taken to optimize the design and minimize biases, there are some limitations due to the naturalistic setting of this study. On the one hand, there are differences in the waiting time, which can be statistically taken into account as covariates in the ANOVA, but cannot be eliminated. The same applies to therapist effects, which can be regarded as a confounding factor, but are not completely eliminated. One reason for this is that it is not yet clear which psychological mechanisms are behind the effects of the therapists, which are more important even in controlled studies than the differences between the treatment conditions [20,36]. Another limitation concerns the implementation check, which is given by self-assessments of the therapists after each session, not by video-based coding of the sessions by independent and blinded raters. Independent session ratings of the quality and the accuracy of the conditions should be realized in future studies, because this can be supposed to have an impact on the outcome, especially in feedback-based therapy sessions.

### Strengths

This study will have a number of strengths. One is the combined process and outcome research, with outcome measures at 4 time points (T1-T4, see the Study Design section) and process monitoring at 2 different sampling rates: session by session with the Bern Patient and Therapist Session Questionnaire in both conditions and high-frequency equidistant time sampling (day by day) in the ASH+SPM condition. Given the 2 sampling rates, the course of micro-outcomes and alliance rates can be aligned (synchronized) with the nonlinear features of change dynamics (eg, critical instabilities, pattern transitions, and within-person synchronization) as they can be derived from the high-frequency time series data. The combination of outcome and process research is still unusual and innovative in RCTs.

Another strength is the strictness of an RCT design implemented in a naturalistic setting, which improves the ecological validity of this study and allows for the transfer to similar settings in outpatient psychotherapy. Third, we will recruit experienced therapists trained in both ASH and SPM (including process monitoring and feedback). As a result, both conditions are performed highly competently and qualify as bona fide therapies. Fourth, we will conduct an implementation review in both study conditions (with the restrictions as noted in the Limitations section). Fifth, in addition to the hypotheses about differential treatment effects (see the Aims of This Study section), mechanisms of change can also be examined.

## Appendix

Multimedia Appendix 1 CONSORT-eHEALTH checklist (V1.6).

Multimedia Appendix 2 Informed consent form.

## Abbreviations

AD: anxiety disorder
ASH: autosystemic hypnotherapy (original German term: Autosystemhypnose)
DSM-5: Diagnostic and Statistical Manual of Mental Disorders [Fifth Edition]
GAD: generalized anxiety disorder
ICD-10: International Statistical Classification of Diseases, Tenth Revision
MDD: major depressive disorder
RCT: randomized controlled trial
SNS: synergetic navigation system
SPM: synergetic process management
TPQ: Therapy Process Questionnaire
